# Effect of a multifaceted educational program for care staff concerning fecal incontinence in nursing home patients: study protocol of a cluster randomized controlled trial

**DOI:** 10.1186/s13063-015-0595-3

**Published:** 2015-03-01

**Keywords:** Fecal incontinence, Nursing homes, Long-term care, Old patients, Care processes, Nursing, Protocol, Cluster-randomized trial

## Abstract

**Background:**

Fecal incontinence has a high prevalence in the older population, which cannot be explained by comorbidity or the anatomical or psychological changes of aging alone. Fecal incontinence leads to a high economic burden to the healthcare system and is an important cause of institutionalization. In addition, fecal incontinence is associated with shame, social isolation and reduced quality of life. The importance of identifying treatable causes in the frail elderly is strongly emphasized. It is recommended that an assessment of fecal incontinence should be implemented as part of an evaluation of older patients. Although there is a substantial evidence base to guide choice of implementation activities targeting healthcare professionals, little implementation research has focused on the care of older people nor involved care processes or care personnel. This study is based on the assumption that fecal incontinence among nursing home patients can be prevented, cured or ameliorated by offering care staff knowledge of best practice through a multifaceted educational program. The primary objective is to test the hypothesis that a multifaceted educational program for nursing home care staff on assessment and treatment of fecal incontinence reduces patients’ frequency of fecal incontinence.

**Methods/design:**

The study is a two-armed, parallel cluster-randomized controlled trial. Primary outcome is the frequency of fecal incontinence among patients. Sample size calculations resulted in a need for a total sample of 240 patients. Twenty nursing home units in one city in Norway will be recruited and allocated to intervention or control by an independent statistician using computer-generated tables. The intervention is a multifaceted educational program. Units in the control arm will provide care as usual. The intervention period is 3 months. Data will be collected at baseline, 3, and 6 months. Data will be analyzed using mixed effect models with the cluster treated as a random effect.

**Discussion:**

This study is the first randomized controlled trial specifically focusing on this neglected area. The result of the study will give evidence for best practice for continence care in nursing homes, and organizational advice concerning implementation strategies.

**Trial registration:**

ClinicalTrials.gov: NCT02183740, registered June 2014.

## Background

Fecal incontinence (FI) is defined by the International Consultation on Incontinence as ‘the involuntary loss of liquid or solid stool that is a social or hygienic problem’ [1]. FI has a higher prevalence in the elderly population than in younger people, which cannot be explained by comorbidity or the anatomical and psychological changes of aging alone [2]. In the nursing home (NH) population, previous studies suggest a prevalence of FI between 10 and 69% [3-5], but it is most often reported to be between 40 and 55% [1,5,6]. The varying prevalence may be due to the lack of a consistent definition of FI, although differences in the quality of continence care in the NHs might also be an explanation [6,7].

FI leads to a high direct and indirect economic burden to the healthcare system, and is an important cause of institutionalization of older patients [1,2,7]. In addition, FI is associated with shame, social isolation and reduced quality of life [1,8,9]. FI among older patients has a more complex etiology compared to the younger population [2,6], and the importance of identifying treatable causes of FI in frail older people, rather than just managing symptoms passively, is strongly emphasized [1]. The level of awareness among health personnel regarding appropriate assessment and treatment options for FI seems limited [1,10-12]. Further, there are indications that both older patients themselves and health personnel consider FI to be a normal part of aging for which nothing can be done [9,11]. It is recommended that an assessment of FI should be implemented as part of an evaluation of older patients [1,2,13].

There is a substantial evidence base to guide choice of implementation activities targeting healthcare professionals in general [14-17]. However, relatively little of the implementation research has focused on the care of older people or involved care processes or care personnel [18]. Even though the evidence is not fully conclusive, implementation research suggests that the most effective method for changing the behavior of health personnel in long-term care settings involves multifaceted educational efforts such as written materials or toolkits combined with individual educational visits, small group training or feedback [14,17,19].

This study is based on the hypothesis that FI among NH patients can be prevented, cured or ameliorated by offering NH care staff knowledge of best practice through a multifaceted educational program on assessment and treatment of FI. The study has been developed according to guidelines for developing and testing complex interventions [20-23]. As there are very few trials either on the treatment of FI in NH patients or on continence education programs for care staff, it was considered necessary to investigate feasibility before evaluating the complex intervention with a randomized controlled trial [20]. Thus, a pilot study was conducted in autumn 2013. The results are not yet published, but the experiences and results have been used in the planning of this cluster-randomized controlled trial.

### Aims and objectives

The overall aim of this study is to achieve a reduction in bowel leakage and accidents for NH patients by altering the quality of continence care among registered nurses (RNs), authorized social educators (ASEs, see below), and care staff in general. The primary objective is to test the hypothesis that a multifaceted educational program for NH care staff on assessment and treatment of FI reduces patients’ frequency of FI.

Secondarily, the trial will investigate the effect of a multifaceted educational program for NH care staff on 1) remission of FI among patients with FI present at baseline or the incidence of new cases of FI among patients identified as continent at baseline; 2) change in NH patients’ FI-related concerns such as mood, constipation, diarrhea and skin condition; 3) increased knowledge among RNs and ASEs; 4) change of practice among RNs, ASEs and care staff in general; 5) and reduction in costs related to FI management. The study also intends to investigate correlates of FI in the NH population.

## Methods/design

The study is a parallel two-armed cluster randomized controlled trial (C-RCT) with a repeated cross-sectional design. As there will be considerable overlap between patients included at the different data-collection time points, some outcomes will be treated as if they come from a cohort design.

### Setting

In Norway, the municipalities have a statuary obligation to provide NH care to those who need it. Most Norwegian NHs are owned and run by the municipalities, and financed by a combination of taxes and patient payment. NH size varies between 20 and 120 beds, divided into units most commonly with 15 beds. NHs are managed by RNs and have an agreement with a general practitioner (GP) who visits the NH once a week. There are no legal requirements for staff-to-patient ratios or specifications for qualifications required for workers [24]. However, NHs have RNs and/or ASEs on duty 24 hours a day, and according to unpublished information from Statistics Norway the staff comprises on average 31% RNs/ASEs, 45% licensed practical nurses (care education on high school level most often before age 18) , and 24% healthcare aides (no vocational health education). Statistics Norway has overall responsibility for official statistics in Norway. In Norway, an ASE has a bachelor’s degree and provides daily care to persons in need, particularly those with intellectual disability, including dementia. ASEs have a defined healthcare and pharmacological competence [25].

### Intervention

The educational program has been developed according to recommendations from implementation research, pedagogic theory and experience from members of the project group [14,16,19,26-31]. A research group comprising four researchers will facilitate the educational program and will be trained as a unified team to enhance standardization of the intervention. Educational content, pedagogical methods and a paper-based guideline for nurse-led assessment and treatment of FI (the FI-guideline, see below) were developed for this study by expert consensus and were evaluated in the pilot study.

#### Content of the multifaceted intervention

*The FI-guideline* is based on best practice recommendations [1,13,32,33] and will be introduced to the RNs/ASEs in the intervention NHs during the workshop (see below). The FI-guideline facilitates a systematic assessment of bowel symptom history and bowel patterns. As FI among NH patients is considered to have a complex etiology, the guideline encourages the RN/ASE to consider a range of possible causes. Examples are loose stools, immobility, cognitive impairment, impaction and use of laxatives. Based on this assessment, the RN/ASE defines a nursing diagnosis, for example: ‘FI related to loose stools, possibly due to excessive laxatives, urgency and reduced mobility. This leads to FI episodes with loose stool and red perineal skin’. The guideline then offers a range of possible interventions. The result of the paper-based assessment, the nursing diagnosis and interventions, is then documented in the patient’s EPR as an individualized care plan.

*One one-day educational meeting* (7 hours) is defined by the Cochrane Effective Practice and Organization of Care (EPOC) as ‘participation of healthcare providers in conference, lectures, workshops or traineeships’ [14]. The educational meeting will be organized as an interactive workshop, which targets knowledge, attitudes, and skills. The workshop will be conducted in a local meeting room in each intervention NH. Part one of the workshop includes the RNs/ASEs filling in a knowledge test (which is part of the data collection). However, by organizing it as a part of the workshop, the pedagogical intention is to facilitate learning, as it is possible to find the answers in the following theoretical input. Part two of the workshop is case-based discussion concerning the FI-guideline. As individualization of the nurse’s diagnoses and the interventions is essential, an important pedagogical intention is to empower the RNs/ASEs’ clinical and critical thinking. Another important issue is how to integrate the use of the guideline with the electronic patient record (EPR) system. The topics for the educational meeting, including the FI-guideline, will be made available for the staff as printed educational material [14].

*A local opinion leader* is defined by EPOC as ‘use of providers nominated by their colleges as educationally influential’ [14]. The opinion leader will be recruited after the educational meeting by the informant method [34] by asking the care manager who is considered to be a principle source of influence. One opinion leader per unit will be recruited. The opinion leader will, together with the care manager, participate in an additional 1.5 hour educational meeting regarding the role of the opinion leader and care manager for this study. They will also receive contact information for the researcher for support during the intervention period. The care manager has responsibility for facilitating adherence to the program and the guidelines in cooperation with the opinion leader.

*Educational outreach* is defined by EPOC as ‘use of a trained person who meets with providers in their practice setting to give information with the intent of changing the providers’ practice’ [14]. The researcher will meet with the healthcare personnel in the practice setting six times for 1.5 hours each time during the 3-month intervention period. The opinion leader will make an agreement with the researcher on how to work and what to focus on between meetings. The NH care staff as a whole is the target group for the educational outreach and will be invited to participate in the educational meetings throughout the intervention period. Facilitating and empowering the staff’s critical and clinical thinking is the main pedagogical approach. The pilot study identified a culture of discontinuity among staff in reporting important clinical observations and decisions in the EPR as an essential barrier to change. In addition, even if decisions were reported in the EPR, it was a problem that staff did not check the patients’ EPR for changes in the patients’ care procedures, which resulted in the patients not receiving the correct interventions for his/her condition. Thus, it will be important to facilitate NH unit-specific strategies to ensure continuity in FI care for the individual patient.

### Control group

The control group will not receive any educational program and will continue with usual care. Data on ordinary practice will be gathered as part of the data collection procedure in this study (health information on patients, ordinary practice as documented in the EPR, care for patients’ FI, diarrhea and constipation as documented in The Fecal Incontinence in Nursing Home Patient questionnaire [6]).

### Eligibility criteria

Results from the pilot study confirmed that units in Norwegian NHs are comparable with the definition by Norton and colleagues [35]. NH units with similar care staff/patient ratios on the day shift and GP coverage will be selected. NH units designated with a specialty or with an enhanced care staff/patient ratio will be excluded. RNs and ASEs working half time or more are eligible for participation in the workshop and to be recruited as opinion leaders in the intervention group. RNs/ASEs working less than half time or only night shifts are excluded. All care staff members in the NH will be invited to the educational outreach meetings throughout the intervention period. All long-term care patients (1 month or more) are eligible for inclusion.

### Recruitment

Approval will be obtained from the director for health and social affairs in the municipality. The first and last authors will participate in a meeting where all managers for the NHs in the municipality will be gathered. The project will be presented and NHs invited to participate. NHs accepting the invitation will be eligible for selection. NH units will be enrolled until the target patient sample size is reached.

### Randomization and allocation

One unit will be defined as one cluster. Two clusters per NH will be recruited. Allocation stages are as follows:NHs will be identified and recruited;Units will be identified and recruited;Patients will be identified;Baseline data collection will take place for units and patients;Allocation will be done by an independent statistician to intervention or control; andRNs/ASEs will be identified and recruited to the intervention (Figure 1).

**Figure 1 Fig1:**
[figure not shown]
**Trial flow-chart.**

The clusters will be allocated to the intervention or control arm using minimization [23]. Minimization factors are a) all units from the same NH will be allocated to the same arm and b) cluster size, where NHs will be sequenced in pairs according to size and then randomized to either intervention or control. The randomization method is simple randomization and is computer generated and performed by an independent statistician (Figure 1).

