### Statistical analyses

Descriptive statistics will be used to present the population and the characteristics of the three groups (units, RNs/ASEs, and patients). As this is a C-RCT, the model of analysis needs to consider the effect of clustering. Analyses must also allow for inclusion of covariates at both the individual and cluster level. Relevant covariates at the individual level in a multiple logistic regression model are age, sex, length of stay in NH, cognitive performance, mobility, functionality, diarrhea, constipation. Hence, this study will use mixed effect models with the cluster treated as a random effect. Analyses will be computed using Stata 12.1.

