#### Primary outcome

As a consequence of the dichotomization of the variable, the primary outcome will be analyzed according to a mixed logistic binominal model. The model will be fitted by maximum likelihood. Because of the relatively high risk of deaths and movement out of clusters, data will be treated as a cross-sectional time series, with the prevalence among all patients present in the cluster at baseline included as a covariate in the analyses.

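### Nursing homes are randomised, but the sample size and the primary model take the unit as the cluster, so correlation between units of one home is left out

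*Protocol article*

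**What the plan says.** Under Randomization and allocation, the article sets the cluster: "One unit will be defined as one cluster. Two clusters per NH will be recruited". The text after Figure 1 then gives two allocation rules: "all units from the same NH will be allocated to the same arm", and "NHs will be sequenced in pairs according to size and then randomized to either intervention or control". The same paragraph names the method as minimization and ends with "The randomization method is simple randomization and is computer generated".

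Sample size uses an average cluster of 15 patients and an ICC of 0.04. It arrives at 103 patients per arm, raised to 120 for dropout, or 240 patients in about 20 units. The ICC sources quoted there (0.038 from the pilot, 0.028 from an epidemiological study) carry no statement of the level at which they were estimated.

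Statistical analyses plans "mixed effect models with the cluster treated as a random effect". For the primary outcome, a mixed logistic model, "The model will be fitted by maximum likelihood", with the cluster's baseline prevalence as a covariate. No home-level random effect, home-level ICC or pair term is described.

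**The concern.** Two units that can never differ in arm are not independent replicates of the treatment. If patients in different units of one home resemble each other more than patients in different homes, that correlation adds to the variance of the treatment comparison. A unit-level design effect and a unit-level random effect both omit it.

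The article itself places some influences at home level. The GP agreement belongs to the home (Setting), and the training of the outcome raters is scheduled per home (Data collection methods). Some positive correlation is therefore plausible.

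At stake are the stated 80% power, the width of the primary confidence interval and the error rate of the primary test. These choices are fixed in this article and conflict with its own allocation rule, so they are not detail left to an analysis plan.

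**Working it through.** **Randomised clusters.** About 20 units / 2 per home = 10 homes. 10 / 2 = 5 homes per arm. 2 × 15 = 30 beds per home.

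**The plan's own figure.** With m = 15 and ICC = 0.04, the design effect is 1 + (15 − 1) × 0.04 = 1.56. The 103 per arm cannot be rebuilt directly, because no control-arm proportion is given for scores 3 to 5. I therefore back out the effective size, 103 / 1.56 = 66.0 per arm, and hold it fixed.

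**Design effect at home level.** For two units per home:

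DE = 1 + (m − 1) × ρ_unit + m × (2 − 1) × ρ_home = 1.56 + 15 × ρ_home

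Here ρ_unit = 0.04 is the correlation within a unit, and ρ_home is the correlation between patients in different units of one home. The documents do not give ρ_home. I assume 0 to 0.04; the top of the range puts all the within-unit correlation at home level. If 0.04 was itself a home-level ICC, the size to use is 30, and 1 + 29 × 0.04 = 2.16, which is the same upper end.

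**Power at the planned size.** Φ[(1.960 + 0.842) × √(1.56 / DE) − 1.960], two-sided 5% assumed.
- ρ_home = 0.01: 2.802 × 0.955 − 1.960 = 0.716, giving 76.3%.
- ρ_home = 0.04: 2.802 × 0.850 − 1.960 = 0.421, giving 66.3%.

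The t column uses the same noncentrality with a noncentral t on 10 − 2 = 8 degrees of freedom.

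**Type I error.** Simulation under the null: 20,000 trials, 10 homes × 2 units × 12 patients (240 / 20), proportion 0.4, total within-unit ICC 0.04, no covariate. A test on unit means stands in for the unit-level mixed model. It is compared with a t-test on home means.

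| ρ_home | DE | n per arm for 80% (66.0 × DE) | Power, normal | Power, t 8 df | Type I, unit t (18 df) | Type I, unit Wald | Type I, home t (8 df) |
|---|---|---|---|---|---|---|---|
| 0 | 1.56 | 103 | 80% | 69.0% | 4.9% | 6.4% | 4.8% |
| 0.01 | 1.71 | 113 | 76.3% | 65.1% | 5.8% | 7.7% | 5.0% |
| 0.02 | 1.86 | 123 | 72.8% | 61.5% | 7.1% | 9.0% | 5.1% |
| 0.03 | 2.01 | 133 | 69.4% | 58.2% | 8.1% | 10.2% | 5.1% |
| 0.04 | 2.16 | 143 | 66.3% | 55.3% | 9.1% | 11.3% | 4.9% |

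The first row separates two effects. With no home correlation, the Wald test is already at 6.4% and the 8-df power already at 69.0%. Those shifts come from having few clusters, not from the wrong level.

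**With the planned baseline-prevalence covariate.** A cluster-mean check with a t reference gave about 7.5–10% without the covariate and about 5–7% with it, depending on how far patients are assumed to keep their status. A maximum-likelihood logistic simulation with a Wald test and the covariate (1,000 replicates) gave 7.8–10.4% if no patient's status persists, 4.5–6.1% if 30% keep it, and 3.2–3.7% if 50% do. One of its three scenarios had a total ICC of 0.08, above the planned 0.04. Persistence is an assumption throughout; the article says only that patient overlap is considerable.

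**The case against.** The strongest reply is the covariate. The primary model adjusts for each cluster's baseline prevalence, and stable differences between homes are partly captured there. With substantial patient overlap the error rate can be close to nominal or below it. This stands. A reader might infer that the planned test is markedly anti-conservative; the documents do not support that without qualification.

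It can also be said that home correlation may be small. Eligibility requires similar day-shift staffing and GP coverage, and no home-level ICC is given. That limits the size but not the point: only zero correlation makes 1.56 right, and the article neither states nor justifies zero. Part of the Wald excess is a few-cluster problem, whose remedy is commonly left to an analysis plan. That is fair too, but the cluster definition, cluster size and level of the random effect are fixed here.

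Three further inferences are tempting and should not be drawn:
- **Far lower power.** Assuming 50% against 35% gives much lower power, but the article states no such rates. At those rates its own 103 per arm and design effect of 1.56 already give only about 41%, so most of that shortfall is a separate question.
- **Lopsided arms.** Simple randomisation of 10 homes could unbalance the arms. But homes are paired by size, and the phrase can be read as the draw within each pair, which forces 5:5. What remains is a labelling fault.
- **Shared manager and staff culture.** The article does not say that units of a home share these. It refers to a ward manager, one opinion leader per unit and unit-specific strategies.

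**Conclusion.** The point holds as a mismatch between the level of randomisation and the level of sizing and analysis. It follows from the article's own text without assumption. The direction for the design effect is certain for any positive correlation between units of one home: 1.56 is too small.

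The size is conditional on an assumed ρ_home of 0.01 to 0.04, and the ranges in the table apply on the protocol's own effective size. With 12 patients per unit instead of 15, the corresponding extremes are 1 + 11 × 0.04 = 1.44 and 1 + 23 × 0.04 = 1.92, a similar relative gap (1.33 against 1.38).

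The type I figures of about 6–9% (t) and 8–11% (Wald) are for an unadjusted analysis. With the planned covariate the net error may be near 5%. That would depend on how many patients stay and keep their status, which the design does not control. A valid primary test should not rest on it.

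**What to change.** - Define the nursing home as the cluster in Randomization and allocation, Sample size and Statistical analyses.
- Fit a random intercept for home with units nested within it, or analyse at home level. Keep the baseline-prevalence covariate.
- Base the primary test and interval on a t reference with degrees of freedom = homes − 2 − home-level covariates: 8 for 10 homes, or 6 if home size and home baseline prevalence are both included.
- Account for home size or pair, since it was used in allocation. A permutation test that respects five pairs is not a workable substitute: with 2^5 = 32 allocations the smallest two-sided p-value is 2/32 = 0.0625.
- Restate the design effect and power at home level, with a stated home-level ICC or a range, rather than enrolling more patients.
- Describe the allocation once, as size-paired randomisation of homes, in place of the two other labels.

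The cost is wording and one extra random effect, wider intervals and a less favourable stated power.
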